### Group 1: self management training program with instructional workbook, video and pedometer

Participants randomly assigned to Group 1 will receive the self management-training program with instructional workbook, video and pedometer at the study centre. All instruction and treatments will be provided by licensed chiropractors. Participants will be scheduled for twelve, 15-min sessions over a 6-week period (two treatment sessions per week). Four weeks following the 6-week treatment period a follow-up treatment (booster) session will be scheduled. Participants will be scheduled as regular patients at the Chiropractic Spine Clinic and Spinal Stenosis Program at Mount Sinai Hospital. All appointments will be confirmed 24 h in advance via telephone or e-mail as preferred by the participant as per usual treatment protocol. The intent is to provide participants with treatment that simulates real practice in terms of scheduling, time spent and content of treatment.

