### Group 2: single instructional session with instructional workbook, video and pedometer

Participants randomized to this group will receive the instructional workbook, video and pedometer provided and explained in a single 15–30 min session with a experienced licensed chiropractor not involved in the provision of the self-management training program. The emphasis on the instructional session is on reviewing the material in the workbook and the structure of the 6 week exercise program. No manual therapy will be provided during the session.

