#### Adverse events

We will measure the presence of adverse events that may be associated with each of the interventions. This will take place following each visit for participants enrolled in Group 1. For participants enrolled in Group 1 and 2, adverse events will be assessed at each follow-up visit. We will define adverse events as an unintended sign or symptom of the intervention. These include: significant increase in back and/or lower extremity pain, numbness, tingling, tiredness or claudication and cauda equine syndrome. We will compute the incidence (95 % CI) of each adverse event listed above. The cumulative number of visits will be used as the denominator. Any adverse event that is life threatening or associated with significant disability will be reported to the Mount Sinai Hospital Ethics Review Board.

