There is a high risk of falls in the LSS population and we need to ensure safety of participants while performing the SPWT. We will train assessors accompanying participants during the SPWT and practice procedures to reduce the risk of falls during the SPWT.

Participants randomized to the single instructional session may not follow the provided instructions, or may perform the exercises incorrectly leading to potential for injury. We will incorporate a safety monitoring protocol and provide participants the opportunity to contact us in an effort to reduce the risk of harm to participants randomized to this intervention.

LSS is a chronic arthritic condition whose prevalence, personal and economic burden is growing exponentially due to the aging population. The vast majority of individuals with LSS receive non-surgical care however, what constitutes effective non-surgical care is unknown. A multi-modal approach with a focus on self-management strategies as outlined in this proposal may be a practical and effective means to improve walking ability, functional status and quality of life in this population.

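### Adverse events per visit cannot be compared between arms that are scheduled for 17 and 5 visits per person and asked about events 17 and 4 times

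*Protocol article*

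**What the plan says.** The Adverse events section of the protocol article sets the measure, "We will compute the incidence (95 % CI) of each adverse event listed above", and then the divisor: "The cumulative number of visits will be used as the denominator". It gives no other denominator and does not define a visit.

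Collection differs by arm. Of adverse-event measurement the section says "This will take place following each visit for participants enrolled in Group 1", and then "For participants enrolled in Group 1 and 2, adverse events will be assessed at each follow-up visit".

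The visit schedule comes from the sections on the two groups and on follow-up:

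- Group 1: "Participants will be scheduled for twelve, 15-min sessions over a 6-week period (two treatment sessions per week"), and then "Four weeks following the 6-week treatment period a follow-up treatment (booster) session will be scheduled".
- Group 2: the materials are "provided and explained in a single 15–30 min session".
- Both groups: four follow-up assessments, at 6 weeks and at 3, 6 and 12 months (Data collection and follow-up; Table 2). The Abstract puts the first at 8 weeks, which does not change the count of four.

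**The concern.** A denominator for comparing harm should be the same kind of quantity in both arms. Here it is a product of the allocation: being assigned to Group 1 adds twelve more treatment contacts than being assigned to Group 2. The numerator also depends on allocation, because Group 1 is questioned at many more occasions.

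Nor is a visit a common unit of exposure. Both arms are followed for 12 months. A Group 1 training session stands for about 3.5 days (6 weeks / 12 sessions), while the 12-month follow-up stands for the six months since the previous one.

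At stake is the safety table. Two incidences with confidence intervals, one per arm, will be read side by side. Their ratio would reflect the visit schedule as much as the harm, and could point the wrong way.

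**Working it through.** **Inputs.** Group 1: 12 sessions, 1 booster, 4 follow-ups. Group 2: 1 session, 4 follow-ups. The arm size is 52, from Sample size.

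**The plan's own figure.** The article states no adverse-event rate or visit total, so there is none to reproduce. The 52 is used only as a head count, and it checks out closely. For 60 % v 30 %, two-sided alpha 0.05 and power 0.8, the pooled-variance formula gives [1.96 × √(2 × 0.45 × 0.55) + 0.842 × √(0.24 + 0.21)]² / 0.30² = 41.97. Then 41.97 / 0.8 = 52.5.

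**Step 1: visits.** Group 1: 12 + 1 + 4 = 17 per person; 17 × 52 = 884. Group 2: 1 + 4 = 5 per person; 5 × 52 = 260. Ratio 17 / 5 = 3.4.

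Because a visit is undefined, other readings are possible:

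| Visits counted | Group 1 | Group 2 | Ratio |
|---|---|---|---|
| All scheduled after randomization | 17 | 5 | 3.4 |
| Only those at which events are asked about | 17 | 4 | 4.25 |
| Treatment visits only | 13 | 1 | 13 |
| All, plus the intake visit | 18 | 6 | 3.0 |
| Common follow-ups only | 4 | 4 | 1.0 |

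Only the last is balanced, and the section does not restrict the count to it.

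**Step 2: one recorded event per affected person (assumption A).** The per-visit ratio equals the per-person ratio divided by 3.4. Group 1 therefore needs more than 3.4 times as many events per person before its rate exceeds that of Group 2. Take 40 % v 20 % of participants affected (assumed rates):

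- Group 1: 0.40 × 52 = 20.8 events; 20.8 / 884 = 2.4 %.
- Group 2: 0.20 × 52 = 10.4 events; 10.4 / 260 = 4.0 %.
- Per-person ratio 2.0; per-visit ratio 2.0 / 3.4 = 0.59.

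The direction reverses. With 208 visits (4 × 52) in Group 2, its rate is 10.4 / 208 = 5.0 % and the ratio falls to 2.0 / 4.25 = 0.47.

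**Step 3: reports proportional to inquiries (assumption B).** Let each inquiry yield a report with probability 5 % in both arms (assumed).

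- Group 1: 0.05 × 884 = 44.2 reports; 44.2 / 884 = 5.0 %.
- Group 2: 0.05 × 208 = 10.4 reports; 10.4 / 208 = 5.0 %, or 10.4 / 260 = 4.0 % if the instructional session is counted as a visit.

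Here there is little or no dilution. The proportion with at least one report over all inquiries (taken as independent) is 1 − 0.95^17 = 58 % v 1 − 0.95^4 = 19 %. At 2 % per inquiry it is 29 % v 8 %; at 10 %, 83 % v 34 %. Arms with the same chance of a report per inquiry look very different per participant, because one is asked more often.

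**Step 4: combined.** Under A the visit denominator favours Group 1. Under B it is close to neutral, and an unrestricted per-participant proportion is biased against Group 1. The document gives no data to place the trial between the two.

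**The case against.** The strongest reply is that no between-arm safety test is planned. The section describes events for each intervention, and risk per visit is a legitimate description of a treatment delivered in sessions. The per-visit rate also partly offsets the unequal questioning, as Step 3 shows. All of this is true. It supports a per-session rate within Group 1. It does not rescue a single visit-based rate given for each arm of a two-arm trial, which readers will compare. Group 2 receives no manual therapy, and the Discussion's worry there is home exercise done wrongly, a risk unrelated to the number of visits.

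The Discussion also promises safety monitoring and a way for Group 2 participants to make contact. That softens the gap in ascertainment but does not make the questioning equal. Life-threatening or disabling events go to the ethics board whatever the denominator.

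A reader might infer three stronger points that the document does not support:

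- **That Group 1 incidence is always diluted three- to fourfold.** This holds only under assumption A. The listed events, such as pain, tingling and tiredness, can recur and be reported repeatedly.
- **That the confidence intervals treat repeated visits by one person as independent.** No interval method is stated, and that detail may properly sit in an analysis plan.
- **That falls are wrongly left off the list.** The article does say "There is a high risk of falls in the LSS population", but it ties this to safety during the walking test and answers it with assessor training. The adverse-event list concerns effects of the intervention.

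**Conclusion.** The point holds as a comparability problem. As written, the plan yields arm-level incidences that depend on the allocated visit schedule (17 v 5, or 17 v 4) and on unequal questioning. With one recorded event per affected person, any per-person ratio of Group 1 to Group 2 between 1 and 3.4 would appear reversed. With reports proportional to inquiries, the per-visit rates would be about equal. The event rates are assumptions, and the totals assume full attendance at 52 per arm. Missed visits would change the totals but would not by themselves make the schedules equal.

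This should be fixed, but it is not critical: the primary endpoint, sample size, randomization and efficacy analysis are untouched.

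**What to change.** For the between-arm safety summary, report by arm the proportion of randomized participants with at least one event of each listed type, with the risk difference and its 95 % CI. Use only events elicited at the four follow-up assessments common to both arms. Both parts are needed: participants as the denominator remove the effect of the visit schedule, and the common follow-ups equalize the number of inquiries.

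Report events elicited at treatment sessions separately, as a rate per session that describes Group 1 only.

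The cost is a few lines of analysis wording, with no extra visits or data. The small downside is that mild, transient events elicited only at treatment sessions drop out of the comparison. They stay visible in the Group 1 description.

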## Discussion

We selected a pragmatic RCT design for our study to reflect a more real world clinical setting. LSS is a varied and multi-faceted condition and in practice, the approach is to tailor care to the patient’s individual needs and tolerances. Participants randomized to Group 1 will receive the standard approach provided at the Spinal Stenosis Clinic at Mount Sinai Hospital; however tailoring will be required with respect to the intensity and type of exercise and manual therapy techniques used, not unlike usual practice. We selected a RCT design because it is the study design of choice when comparing the effectiveness of interventions.

We considered the SPWT to be the appropriate primary outcome measure to address our primary aim. The SPWT is the current gold standard for measuring objective walking capacity in LSS as it assesses walking ability in a real life setting [43]. We also included the functional scale of the ZCQ which is a self-report measure of walking ability that is highly correlated (*r* = 0.80) to the SPWT [31]. The SPWT is logistically more challenging to perform because of the need of a large walking area and added personnel, time and expense of conducting the test, and added time, expense and inconvenience for participants travelling to the study site for follow-ups. This may result in a higher dropout rate for follow-up assessments. To mitigate this possibility of non-compliance to follow-up SPWTs we included the self-report functional scale of the ZCQ that can easily be assessed by phone. Moreover, we can compare our findings to other studies using this self-report outcome measure.

At our centre we have two long and wide hallways connected by two shorter hallways forming a large rectangular area (140 m long) where participants easily can perform the SPWT.

However, the SPWT has a ceiling effect in that the test measures distance traveled for a maximum of a 30-min period. For this reason we will only include participants who are more severely impaired and cannot complete the SPWT during the baseline assessment.

We have included a 1-month booster session following the 6-week training program. This emulates our current practice protocol at our Spinal Stenosis Clinic at Mount Sinai Hospital. The rationale being that LSS is a chronic condition and patients may benefit from periodic monitoring of their self-management skills and abilities. Periodic reassurance and positive reinforcement may also be of benefit especially among patients with underlying psychosocial barriers such as poor coping skills that accentuate functional limitations. Periodic monitoring and coaching may help to improve longer-term outcomes.

A leading cause of failure of RCTs is the lack of enrollment of sufficient number of participants into the study. We have enlisted a large referral source for potential participants. LSS is a very common condition seen by neurosurgeons and orthopedic spine surgeons, rheumatologists, physiatrists, family physicians and chiropractors. If our enrollment is deemed slow, we will expand our referral source to the University of Toronto vascular surgeons who also see a large number of patients with neurogenic claudication caused by LSS. We will also advertise in local newspapers and seniors publications. In addition, we will distribute pamphlets to be placed in-patient waiting areas at participating hospital clinics and in community clinics. Compliance to follow-ups may be problematic and we plan to provide incentives in the form of covering transportation costs up to $25 per day.

We anticipate that assessor blinding (to assigned intervention) during follow-up assessments will be challenging. We will implement strict rules preventing the communication, regarding participant allocation among participants, the research coordinator and blinded assessors.

Study design limitations include the lack of blinding of both practitioners and patients and this can introduce bias. The multi-modal and pragmatic nature of the design prohibits the determination of the component(s) of the intervention that may be responsible for potential improvements. There is potential for participants to receive other interventions during the intervention and between follow-up periods, which may impact the results. We will compare co-interventions receive between group and comment on the potential impact they may have on the results.

There is a high risk of falls in the LSS population and we need to ensure safety of participants while performing the SPWT. We will train assessors accompanying participants during the SPWT and practice procedures to reduce the risk of falls during the SPWT.

Participants randomized to the single instructional session may not follow the provided instructions, or may perform the exercises incorrectly leading to potential for injury. We will incorporate a safety monitoring protocol and provide participants the opportunity to contact us in an effort to reduce the risk of harm to participants randomized to this intervention.

LSS is a chronic arthritic condition whose prevalence, personal and economic burden is growing exponentially due to the aging population. The vast majority of individuals with LSS receive non-surgical care however, what constitutes effective non-surgical care is unknown. A multi-modal approach with a focus on self-management strategies as outlined in this proposal may be a practical and effective means to improve walking ability, functional status and quality of life in this population.
